## Abstract

**Introduction:**

Adolescent physical activity promotion is rarely effective, despite adolescence being critical for preventing physical activity decline. Low adolescent physical activity is likely to last into adulthood, increasing health risks. The Get Others Active (GoActive) intervention is evidence-based and was developed iteratively with adolescents and teachers. This intervention aims to increase physical activity through increased peer support, self-efficacy, group cohesion, self-esteem and friendship quality, and is implemented using a tiered-leadership system. We previously established feasibility in one school and conducted a pilot randomised controlled trial (RCT) in three schools.

**Methods and analysis:**

We will conduct a school-based cluster RCT (CRCT) in 16 secondary schools targeting all year 9 students (n=2400). In eight schools, GoActive will run for two terms: weekly facilitation support from a council-funded intervention facilitator will be offered in term 1, with more distant support in term 2. Tutor groups choose two weekly activities, encouraged by older adolescent mentors and weekly peer leaders. Students gain points for trying new activities; points are entered into a between-class competition. Outcomes will be assessed at baseline, interim (week 6), postintervention (week 14–16) and 10-month follow-up (main outcome). The primary outcome will be change from baseline in daily accelerometer-assessed moderate-to-vigorous physical activity. Secondary outcomes include accelerometer-assessed activity intensities on weekdays/weekends; self-reported physical activity and psychosocial outcomes; cost-effectiveness and cost-utility analyses; mixed-methods process evaluation integrating information from focus groups and participation logs/questionnaires.

**Ethics and dissemination:**

Ethical approval for the conduct of the study was gained from the University of Cambridge Psychology Research Ethics Committee. Given the lack of rigorously evaluated interventions, and the inclusion of objective measurement of physical activity, long-term follow-up and testing of causal pathways, the results of a CRCT of the effectiveness and cost-effectiveness of GoActive are expected to add substantially to the limited evidence on adolescent physical activity promotion. Workshops will be held with key stakeholders including students, parents, teachers, school governors and government representatives to discuss plans for wider dissemination of the intervention.

**Trial registration number:**

ISRCTN31583496.

Strengths and limitations of this studyThe strengths of the GoActive evaluation study include the cluster randomised controlled trial design, objective measurement of physical activity, long-term follow-up and testing of causal pathways to rigorously assess the effectiveness and cost-effectiveness of the GoActive programme.We will recruit 16 secondary schools from both Essex and Cambridgeshire. A possible limitation of the study is that, despite our purposive sampling of schools with varied socioeconomic status, it is likely that participants may not be entirely representative of the wider UK population (particularly with regards to ethnicity).

## Background

Physical activity is protective against obesity and related metabolic disorders in young people.^1 2^ Meta-analytic data from 20 871 4–18-year-olds suggest that every 10 min increase in moderate-to-vigorous activity (MVPA) is associated with a smaller waist circumference (−0.52 cm) and lower fasting insulin (−0.028 pmol/L).^2^ In adolescence, physical activity declines 7% per year.^3^ Low physical activity in adolescence is also likely to progress to adulthood inactivity,^4^ increasing the risk of diabetes, cancer and mortality.^5 6^ Adolescence is therefore a critical period to increase physical activity,^7^ both due to the aforementioned decline and because pubertal, brain and social development during this time leads to new capacity for changing health behaviours,^8^ increasing the likelihood of long -term change.

The 2012 Chief Medical Officer’s report states the importance of physical activity among young people^9^ and a recent international expert panel concluded that developing effective and sustainable interventions to increase physical activity among young people is the most important priority in the physical activity research field.^10^ Further, the recently published report from the All-Party Commission on Physical Activity calls specifically for the creation of active schools, including the provision of a more diverse and inclusive offer of physical activity.^11^

Reviews highlight the limited efficacy of existing adolescent physical activity promotion interventions.^12–15^ We have previously identified several possible reasons for this lack of effectiveness^16^; for example, many interventions only target subgroups (such as girls^17^ or low socioeconomic groups)^18^ despite activity declining among all groups.^16^ We aim to recruit the whole school year group for evaluation, and to target all groups in the Get Others Active (GoActive) intervention, which to our knowledge has rarely been done in physical activity promotion interventions. In addition, the decline in activity mainly occurs out of school^16^; however, many interventions only target specific school-based times; for example, school time^13 19^ or Physical Education (PE) lessons,^20^ whereas GoActive encourages participants to do more activity both in and out of school. Further, very few adolescent physical activity interventions, especially among older adolescents, have been evaluated using objective measurement of physical activity,^14^ and include long-term follow-up, process evaluation or an assessment of cost-effectiveness.^21^ This therefore highlights an urgent need for more rigorous evaluation of potentially effective strategies to increase physical activity in adolescents.

### Objectives

The primary aim of this study is to assess the 10-month effectiveness of the GoActive intervention to increase average daily objectively measured MVPA among 13–14-year-old adolescents. We will also assess the effect of GoActive immediately postintervention, and on the following secondary outcomes: (1) objectively assessed activity intensities during school time, weekday evenings and weekends; (2) student-reported physical activity participation, self-efficacy, peer support, social networks, self-esteem, friendship quality (proposed mediators) and well-being, and school-level attendance and academic performance; and (3) body composition (body fat percentage and body mass index (BMI) z-score). We will investigate potential moderation of intervention effects by sex, socioeconomic status, ethnicity, baseline activity level and weight status, and potential mechanisms of effect by proposed mediators using a mixed-methods approach. Further, we will assess short-term (within-trial) and potential long-term cost-effectiveness of the GoActive intervention and will conduct a comprehensive process evaluation including questionnaires, focus groups, and individual interviews (with participants, mentors, teachers, and intervention facilitators), data from intervention logs and website analytics.

## Intervention

The development of the GoActive intervention with supporting rationale has been described in detail previously.^22^ Briefly, each year 9 class (tutor group or home room class) chooses two activities each week from a selection provided. There are currently 20 activities available, using little or no equipment, and appealing to a wide variety of students (including Ultimate Frisbee, Zumba and Hula Hoop). Materials available on the password-protected GoActive intervention website include activity instructions (Quick Cards) which offer an overview of each activity, a short explanation, suggestions for adaptations and provide advice, safety tips and ‘factoids’, in addition to a short video introducing each activity. GoActive is implemented using a tiered-leadership system where mentors (older adolescents within the school) and peer leaders (within each year 9 class) encourage students to try these activities each week. The mentors remain paired with each class for the duration of the intervention, whereas the peer leaders (two per class each week, one male and one female) change every week. In addition to the student leaders, a local authority-funded intervention facilitator will support the programme during the first term of delivery and will provide distant support thereafter.

Teachers are encouraged to use one tutor time weekly to do one of the chosen activities as a class; however, students gain points for trying these new activities at any time in or out of school. Points are gained every time they try an activity; there is no expectation of time spent doing the activity as points are rewarded for the taking part itself. Individual students keep track of their own points privately on the study website and their points are entered into the between-class competition. Class rankings are available on the website to encourage teacher support and students receive small rewards (such as a sports bag, t-shirt, or hoodie) for reaching individual points thresholds.

## Methods

### Study design

We will conduct a school-based cluster randomised controlled trial (CRCT) of the GoActive intervention. The study will be conducted in government-funded, non-fee-paying (state), all-ability, co-educational secondary schools including year 9 students in Cambridgeshire and Essex, UK. After baseline measurements (September–December 2016), schools will be randomly allocated to one of two conditions: (1) to deliver the GoActive intervention to the whole of year 9 or (2) to a no-treatment control group. Participant data collection will occur at baseline, 6 weeks, 14–16 weeks and 10 months (primary outcome). The protocol will be conducted and reported in accordance with Standard Protocol Items: Recommendations for Interventional Trials (SPIRIT) guidance (see online supplementary data 2).^23–25^

10.1136/bmjopen-2016-014419.supp2Supplementary data 2

## Recruitment procedures

### Schools

We will recruit 16 secondary schools with a mixture of socioeconomic status, representative of UK variability. Head teachers, year 9 leaders and PE leaders from all eligible schools will be sent an invitation letter and school information sheet via email. These documents will describe the study procedures (eg, student recruitment and consent, measurements) and will include an electronic link to an information video describing GoActive. A follow-up phone call to each school will be made approximately 1 week after the initial invitation, asking for a meeting with relevant staff to discuss the study and request consent to participate. Phone calls and repeat emails will continue until 16 schools (8 in Cambridgeshire and 8 in Essex) have provided consent to participate. We will also create a waiting list to replace any schools who may withdraw from the study prior to randomisation. We will also use our existing networks and school contacts to facilitate school recruitment. Schools that do not agree to take part will be asked to select the most relevant reason for their refusal from a predetermined list (eg, lack of interest, lack of time).

### Participants

All year 9 students (13–14 years) in participating schools will be eligible to participate in study measurements. As in feasibility and pilot work, we plan to include participants with a disability and those with learning or movement difficulties, taking care to follow advice from schools.^26^ This is appropriate due to the inclusive nature of the GoActive intervention and will help to avoid stigmatisation of any groups within schools.^27^ As such, no exclusion criteria will be applied.

All year 9 students and their parents will receive a paper invitation pack, including a participant information sheet and an invitation to participate in study measurements. These information packs will be distributed to students during an introductory assembly conducted by a member of the GoActive team; students will be asked to take the packs home to their parents. Parents will also be sent duplicate information via email (‘ParentMail’ or the appropriate equivalent system as agreed by the school). Parents will be asked to provide passive consent (active opt-out consent) for their child to take part in study measurements. We will give parents at least 2 weeks to respond (a final date for response will be included in all correspondence). After 1 week, parents will receive an additional copy to ensure further opportunity for opting out prior to study measurements. Parents will be given the option to phone or email the study team (in lieu of returning a form) to facilitate their ability to respond. Reminders will additionally be included in all relevant school media, including regular newsletters sent from the school. Written assent will be obtained from the students by research assistants trained in Good Clinical Practice prior to any baseline measurements taking place. Approved consent forms will be available on the study website http://www.goactive-uk.com. Mentors and teachers will provide written consent or assent (for those older and younger than 16 years, respectively) to participate in process evaluation following the same procedures as study participants.

Parental opt-out responses ranged from 2 (<1%) to 18 (7%) in feasibility and pilot schools, with 72%–88% of eligible students assenting to participate.^26^ Recruitment rates using this strategy are substantially higher than previous UK-based research in this age group using parental opt-in consent (23% of eligible participants).^7^ Participants will be informed that they can discontinue all or any part of the study (either or both measurements and intervention) at any time at their or their parent/guardian’s request.

## School randomisation

Schools will be stratified based on Pupil Premium (proxy for socioeconomic status, below/above the county-specific median; for information: https://www.gov.uk/guidance/pupil-premium-information-for-schools-and-alternative-provision-settings) and county (ie, Cambridgeshire or Essex). Randomisation lists for each stratum will be prepared by a statistician, using Stata (ref: StataCorp. 2015. Stata Statistical Software: Release 14. College Station, Texas, USA: StataCorp), after baseline measurements are completed to ensure schools and participants are unaware of their group allocation at baseline. Eight schools will be randomised to deliver the GoActive intervention and eight to a no-treatment control condition. For measurements after randomisation, it will not be possible to blind participants to randomised allocation as the intervention schools will have received the GoActive intervention.

Measurement staff will be blinded to intervention condition throughout the study as they will be trained and work separately from those involved in intervention delivery. Process evaluation with measurement staff will examine the success of blinding.

### Control condition

The control group will receive no-treatment or ‘usual care’, and no intervention will be implemented. If we were to offer the control group the intervention after follow-up measures, it would prevent us from potentially assessing longer-term impact of the programme. As such, this study has no waitlist control condition.

## Data collection

Measurements will be conducted at four time points by trained researchers (figure 1). The primary measure of intervention effectiveness will be change from baseline in accelerometer-measured average daily MVPA at 10-month follow-up. All primary and secondary outcomes will be assessed at T1 and T4. Anthropometric measures will be removed from T3 (which will include all other outcomes, i.e. accelerometry and questionnaire-based measures), and T2 will focus on assessing the questionnaire-based measures only (including mediators of change). To prevent artificially inflated school-level clustering (due to weather conditions or school events) and facilitate recruitment and retention, measurements at each school will be staggered over ≥2 weeks using a predetermined schedule.

**Figure 1 F1:**
[figure not shown]
Measurement sessions included in the GoActive evaluation.*All measures include accelerometry, anthropometry and outcomes questionnaire (student-reported physical activity participation, self-efficacy, peer support, group cohesion, self-esteem, friendship quality, and mood).

### Accelerometry

The primary outcome will be accelerometer-assessed change in average daily MVPA between baseline and 10-month follow-up. Secondary accelerometry outcomes will be change from baseline in average minutes spent in sedentary and light activity, as well as overall physical activity (counts per minute) during school, weekdays after school and at weekends.

Participants will be asked to wear a wrist-worn Axivity AX3 monitor at T1, T3 and T4. Participants will be asked to wear the monitors on a strap on their non-dominant wrist, continuously for seven consecutive days (including when in water and when asleep). Wrist-worn monitors have been validated for use among children and adolescents, in laboratory and free-living environments, and to assess physical activity, sedentary time and postural allocation.^28–30^ There is evidence to support the increased acceptability and higher compliance rates of wrist-worn monitors compared with waist-worn monitors.^31–37^ To further optimise accelerometer-wear compliance, we have developed a monitor wear and return protocol which is led by researchers (and not teachers) and includes regular reminders and an incentive (eg, GoActive-branded headphones, GoActive-branded pens). We have previously successfully applied this protocol in adolescent cohort studies to obtain high levels of valid accelerometry data (ROOTS: 825/930–89%^7^; SPEEDY-3: 428/480–89%^16^).

Throughout data collection, we will continuously monitor response rates and take appropriate action (eg, requesting teacher involvement) if it drops <70% for the primary outcome. In cases where participants do not return their accelerometer after frequent requests, they may not be issued a monitor at subsequent measurements, but will be allowed to continue their participation in the study and all other (secondary) measures. This is to prevent excessive monitor loss. We deem this appropriate as sample size calculations indicate that we will retain 95% power should retention drop to 55% (80/150 participants predicted to participate in each school based on pilot data).

Once returned, data (continuous waveform data) from the accelerometers will be downloaded. Non-wear time with a minimum duration of 60 min will be removed; the acceleration threshold for identifying non-worn time will be based on visual inspection of the data.^38 39^ As we will use a 24-hour protocol, we plan to apply a diurnal adjustment to reduce any bias that may occur if data were not fully representative of a 24-hour period but will also allow full use of the data collected.^40^ For any daily analysis, we will set minimum criteria to ensure hours are equally distributed across whole day.^40^

Continuous waveform data will be converted to be comparable to cut-points used previously for ActiGraph accelerometers used to classify time spent sedentary (equivalent to ≤100 ActiGraph cpm) or in light (equivalent to 101–1999 ActiGraph cpm), moderate–vigorous (equivalent to ≥2000 ActiGraph cpm) or appropriate vector magnitude equivalents.^41–43^ Monitor output will be reviewed prior to analysis to confirm that these decisions are appropriate for the population and monitor applied. Further, we will consult physical activity measurement experts to ensure we can be aware of relevant new methodology and apply where appropriate. Algorithms to identify sleep time are constantly in development. Given that we are operating a 24-hour wear time protocol, we will use the most up-to-date sleep identification algorithms to remove sleep time when estimating physical activity intensities (particularly sedentary time).

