## Analyses

### Sample size

We aim to detect a 5 min difference in change in MVPA per day at 10-month follow-up, as observed in the pilot study.^26^ A 5 min increase is relevant at population level as it would increase the proportion of adolescents meeting the guidelines of 60 min of MVPA per day from 43% to 50% (based on baseline pilot data), with significant impact on population health.^2^ To estimate the required sample size, the following parameters have been used: power=85%, significance level=5%, SD=17.8 (observed in the GoActive pilot),^26^ intraclass correlation coefficient=0.034 (observed in SPEEDY-3, n=57 schools),^43^ correlation between baseline and follow-up MVPA=0.59 (observed in GoActive pilot, to account for adjustment for baseline MVPA)^26^ and average cluster size=100. Based on these parameters, we estimate n=1310 participants will be required for the primary effectiveness analysis. To account for potential school dropout and an estimated loss-to-follow-up of 30%–40%, we aim to recruit 16 schools with 150 participants (total n=2400; average recruitment per school in pilot=154).^26^ Should a school have >150 students in year 9, we will include all those who assent to measurement.

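### The 95% power stated for 55% retention does not follow from the protocol's own inputs, which give about 90%

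*Protocol article*

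**What the plan says.** The Sample size section sets the target: "We aim to detect a 5 min difference in change in MVPA per day at 10-month follow-up, as observed in the pilot study". Its inputs are "power=85%, significance level=5%, SD=17.8 (observed in the GoActive pilot"), "intraclass correlation coefficient=0.034 (observed in SPEEDY-3, n=57 schools"), "correlation between baseline and follow-up MVPA=0.59 (observed in GoActive pilot, to account for adjustment for baseline MVPA") and an average cluster size of 100. From these, "we estimate n=1310 participants will be required for the primary effectiveness analysis". Recruitment is set at 16 schools of 150 (2400 students) to cover school dropout and a 30%–40% loss to follow-up. The School randomisation section allocates eight schools to each arm.

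The Accelerometry section covers students who do not return a monitor after repeated requests: "they may not be issued a monitor at subsequent measurements". Its purpose is to limit monitor loss. The protocol judges this acceptable because, by its sample size calculations, "we will retain 95% power should retention drop to 55% (80/150 participants predicted to participate in each school". No separate inputs are given for that figure.

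**The concern.** The required sample was set for 85% power, yet the Accelerometry section reports 95% after almost half of the recruited students have been lost. The Sample size section contains the only calculation in the document, so the 95% can be tested against it.

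The figure has a function. It is the stated reason why losing later primary-outcome data from some students is tolerable. If it is too high, readers will think that the trial has more room for missing accelerometry than it has.

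**Working it through.** **Inputs.** From Sample size: difference 5 min/day, SD 17.8, correlation 0.59, ICC 0.034, alpha 5%, planned power 85%, cluster size 100. From School randomisation: 8 schools per arm. From Outcome analyses: adjustment for baseline MVPA, a 95% CI, and robust standard errors by school. Sidedness is not stated. Two-sided is taken here because it fits the 95% CI and, as step 1 shows, reproduces 1310.

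**Step 1: reproduce the 1310.**
- Baseline-adjusted variance: 17.8² × (1 − 0.59²) = 206.5, so the adjusted SD is 14.37.
- Students per arm without clustering: 2 × 206.5 × (1.960 + 1.036)² / 5² = 148.4. This rounds up to 149, or to 150 with the usual t correction.
- Design effect at 100 per school: 1 + 99 × 0.034 = 4.366.
- Total: 2 × 149 × 4.366 = 1301, or 2 × 150 × 4.366 = 1309.8. The second is the stated 1310.

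**Step 2: same method at 80 analysed per school, 16 schools.**
- Design effect: 1 + 79 × 0.034 = 3.686.
- SE of the difference: √[2 × 206.5 × 3.686 / (8 × 80)] = 1.542 min.
- 5 / 1.542 = 3.242. Normal power: Φ(3.242 − 1.960) = 0.900.
- Noncentral t with 16 − 2 = 14 df: 0.854.

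**Step 3: other retention levels, 8 schools per arm.**

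| Analysed per school | Normal | t, 14 df |
|---|---|---|
| 80 (53.3% of 150) | 90.0% | 85.4% |
| 82.5 (55% of 150) | 90.2% | 85.7% |
| 100 | 91.5% | 87.2% |
| 150 (no loss) | 93.3% | 89.5% |

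On the normal basis, 95% needs about 297 analysed students per school. With 14 df it is not reached at any cluster size; the limit is about 93.9%.

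**Step 4: could another convention explain 95%?**

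| Convention | Implied N at 85% power | Power at 80 per school (normal) |
|---|---|---|
| Two-sided, baseline-adjusted | 1301–1310 | 90.0% |
| One-sided, baseline-adjusted | 1039 | 94.5% |
| One-sided, change score | 1310 | 89.4% |
| Two-sided, change score | 1633 | 82.4% |
| Variance factor (1 − r) in place of (1 − r²) | 815 | 98.3% |

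None of these gives both 1310 and 95%. An ICC of about 0.025 would give 95% at 80 per school (normal), but the protocol states only 0.034.

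**Step 5: school dropout.** With 7 schools per arm and 80 each, the SE is 1.649 and power is 85.8% (normal) or 79.5% (12 df).

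**The case against.** The best defence is that the protocol gives neither the inputs behind 95% nor the sidedness of the test, and that a one-sided 5% test gives 94.5% at 80 per school. This does not rescue the sentence. Under the planned baseline-adjusted analysis a one-sided test needs 1039 students, not 1310, and it sits poorly with a 95% CI.

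A second objection is that 14 degrees of freedom is a reviewer's choice, since the protocol says only that standard errors will be robust. That stands: the type II error to set against the stated 5% is 10%, and the 15% on 14 df is a supplementary figure.

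Three stronger readings are tempting, and the document does not support them.
- *16 × 80 = 1280 is below 1310, so the two sections contradict each other.* They do not on that account. The 1310 assumes clusters of 100, which is about 13 schools. Spreading 1280 over 16 schools lowers the design effect from 4.366 to 3.686, and power is higher (90.0% against 85.4%, both normal).
- *On 14 df the margin over the 85% target is nil.* This compares unlike quantities, because the 85% target was not computed on cluster-level df. Like for like, 13.1 schools of 100 have about 85% (normal) or 78% (11 df), against 90.0% or 85.4% for 16 schools of 80. The margin is about 5 to 7 points.
- *The power argument should be withdrawn.* With all 16 schools, power at 80 per school still meets 85% by either method, and the policy's stated purpose is to limit monitor loss. The argument needs a corrected figure.

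It is also fair that 93.3% with no loss is only 1.7 points short of 95% on the normal basis, and that schools with more than 150 students will contribute all who assent.

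**Conclusion.** The sentence is wrong as written. On the calculation that reproduces the protocol's own 1310, power with 80 analysed students in each of 16 schools is about 90%, so the type II error is about 10%, twice the 5% implied. With 14 cluster-level df, power is about 85%. Even no loss from 150 per school falls short of 95%.

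This rests on a two-sided 5% test, equal cluster sizes, the stated ICC and all 16 schools being retained. That 95% is a slip for 85% is possible, but the document gives no evidence for it. The mismatch between 55% and 80/150 (53.3%) is minor and moves power by about 0.2 points.

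Severity is moderate. The 1310, the recruitment target and the analysis all stand, and the tolerance for monitor-related loss remains defensible if essentially all schools stay. With two schools lost, power is only just above 85% on the normal basis and below it with 12 df.

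**What to change.** In the Accelerometry section, replace the 95% statement with wording such as: *with all 16 schools and 80 analysed students per school (53% retention), power is about 90% by the normal approximation and about 85% with 14 degrees of freedom*. If 95% came from different inputs, state them, including the sidedness of the test and the ICC, and reconcile them with the Sample size section.

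Rest the tolerance for monitor-related loss on the corrected figure, and add that it depends on keeping essentially all schools: with 7 per arm and 80 each, power is about 86% (normal) or 79% (12 df).

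The cost is a change of wording and a less favourable published figure. No extra schools, students or analyses are needed.
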